# RISE for recovery after acute whiplash injury: protocol for a randomised feasibility trial of a clinician-supported SMS-based behavioural intervention

**DOI:** 10.1136/bmjopen-2026-123039

**Published:** 2026-09-11

**Keywords:** PAIN MANAGEMENT, Musculoskeletal disorders, Psychological Stress, Randomized Controlled Trial

## Abstract

**Introduction:**

Whiplash-associated disorders (WADs) are the most common and costly consequence of road traffic injury (RTI). Providing early and effective treatment is a healthcare priority; however, current guideline-based care which focuses on education and physiotherapy-led exercise does not routinely address the psychosocial effects of trauma, and access to early integrated treatment is limited. This study aims to evaluate the feasibility of delivering and evaluating recovery, information, support and empowerment (RISE), a co-designed short message service-based intervention integrating psychosocial and exercise/activity support for individuals with acute whiplash injury who are at risk of poor recovery in a randomised feasibility trial. Secondary aims are to explore preliminary changes in candidate clinical outcomes and opportunities for intervention personalisation and future implementation.

**Methods and analysis:**

This mixed-methods randomised controlled feasibility trial with a nested process evaluation will recruit 50 participants (>18 years) with WAD grade II/III who are identified at medium to high risk of poor recovery and within 12 weeks of RTI from Queensland emergency departments and the community. Participants will be randomised in a 1:1 ratio to receive either the RISE intervention (tailored, daily messaging+optional brief clinician support session/s) or an active control (general health-related text messages plus access to an online resource, My Whiplash Navigator). Feasibility outcomes, including recruitment and retention rates, data collection (including wearable-derived and economic data) and intervention uptake will be descriptively summarised and evaluated against pre-defined traffic light progression criteria. Acceptability will be examined using validated questionnaires and purpose-built items, qualitative interviews with intervention participants and focus groups with patients, clinicians and funders. Secondary aims will be addressed through preliminary estimates of between-group differences in patient-reported outcomes with 95% CIs and exploratory analysis of multimodal data (eg, wearable-derived physiological data, intervention engagement metrics) using a large language model where possible to inform future personalisation and implementation planning.

**Ethics and dissemination:**

This trial is approved by the Townsville Hospital Human Research Ethics Committee (HREC/QTHS/121395) and ratified by the Human Research Ethics Committee at The University of Queensland, which is the study sponsor (2025/HE002491). Results will be published in peer-reviewed journals and presented at conferences and professional meetings.

**Trial registration:**

ACTRN12626000506392; date registered: 23 April 2026; https://www.anzctr.org.au/Trial/Registration/TrialReview.aspx?id=390706&isReview=true

STRENGTHS AND LIMITATIONS OF THIS STUDYFirst of its kind feasibility evaluation of a short message service-based intervention to support recovery after whiplash injury following road traffic crashes.Participant-masked and assessor-blinded randomised controlled trial design to assess feasibility outcomes against a pre-specified traffic-light framework, supporting transparent decision-making regarding progression to a larger definitive trial.A nested qualitative study enables triangulation of quantitative feasibility data with in-depth participant perspectives on intervention experience and delivery.The recovery, information, support and empowerment intervention was co-designed with patients, clinicians and insurance representatives, enhancing methodological relevance, acceptability and implementation fidelity.The intervention targets individuals at medium to high risk of poor recovery within 12 weeks of injury, which may limit methodological generalisability to later stages of recovery.

## Introduction

 Providing early and effective treatment for whiplash-associated disorders (WAD), the most common and costly consequence of road traffic injury (RTI), is a healthcare priority. Currently, clinical guidelines for WAD treatment recommend education and exercise/activity in the first 12 weeks after injury.^1^ However, these approaches demonstrate only modest and short-term benefits.^2–4^ More than one-third of people, particularly those at high risk of poor recovery, do not fully recover and continue to experience persistent pain and disability beyond the acute phase.^5^ Ongoing symptoms are frequently accompanied by psychological comorbidities, including post-traumatic stress disorder, which further complicate recovery trajectories.^6^

Targeted approaches that address the psychological effects of trauma and modifiable psychological risk factors alongside guideline-based care are increasingly recognised as important for improving recovery and well-being following RTI.^7^ There is substantial evidence for the role of psychological factors in recovery from WAD^8–10^ as well as the broader psychological impacts associated with the lived experience of RTI.^11
12^ Notably, an early integrated psychological and physiotherapy exercise intervention targeting individuals at risk of poor recovery has been shown to improve pain-related disability compared with exercise alone in patients with acute WAD, with effects maintained at 12 months.^13^ Secondary analysis of this clinical trial indicated that reductions in stress symptoms and improvements in pain-related coping represented key pathways through which this intervention exerted its effects on disability.^14^ However, timely access to early targeted care remains limited, and there is a need for complementary approaches that are low-intensity, cost-effective and scalable within routine clinical pathways, including compensation-based healthcare systems.

Digital health interventions offer an opportunity to deliver early, scalable and accessible support following injury. One promising approach is the use of short message service (SMS)-based interventions, which are increasingly used in healthcare settings and require minimal digital literacy.^15^ SMS interventions have been shown to be effective and acceptable in promoting behaviour change, improving self-management and supporting recovery across a range of chronic health conditions (eg,^16
17^). Emerging evidence suggests that SMS interventions may also be beneficial in the management of musculoskeletal pain; however, there are few high-quality studies in this area,^18^ and limited research has incorporated co-design methods to tailor SMS interventions to patient and clinician needs, preferences and lived experience.^19^ To date, the potential of SMS-based interventions to support recovery in individuals with WAD and the potential to integrate digital technologies, such as wearable devices and human-centred artificial intelligence to enhance personalisation and optimisation of early integrated care has yet to be examined.

The primary aim of this study is to evaluate the feasibility of delivering and evaluating recovery, information, support and empowerment (RISE), a co-designed SMS-based early intervention to improve recovery for individuals with WAD who are at risk of poor recovery within the first 12 weeks following a RTI, evaluated in a randomised controlled feasibility trial. The RISE intervention includes daily personalised text messages and optional brief psychologist and physiotherapy support. It will be compared with an active control condition comprising general health-related text messages plus access to an online resource, *My Whiplash Navigator,* to facilitate participant blinding. Feasibility will be assessed in terms of recruitment, retention, intervention engagement, collection of wearable-derived and cost data and acceptability. Pre-defined criteria, interpreted alongside the qualitative process measures from patients, clinicians and funders, will guide decisions regarding progression to a future definitive trial. Secondary aims are to: (1) explore possible preliminary changes in candidate patient-reported clinical outcomes comparing RISE with an active control condition and (2) explore the feasibility of analysing multimodal data, including wearable-derived physiological metrics (eg, activity and sleep), patient-reported outcomes and intervention engagement data using a large language model to generate insights to inform future intervention personalisation and optimisation. Findings from this study will inform the need for and design of a future definitive trial.

## Methods and analysis

### Study design and setting

This is a mixed-methods randomised controlled feasibility trial with blinded outcome assessment. Fifty adults with acute WAD (<12 weeks post-injury) who are at medium or high risk of poor recovery will be randomly allocated 1:1 to either the RISE intervention or active control (25 per group^20^). Participants will be recruited through three Queensland-based metropolitan hospital emergency departments (ED), including Sunshine Coast University Hospital, Princess Alexandra Hospital (PAH) and Metro North Virtual Emergency Care Services (VECS). Recruitment will also occur through community channels, including social media, digital marketing and local clinics, to ensure the target sample size is reached.

Participant blinding will be supported by providing both groups with SMS contact without disclosing group allocation; however, full participant blinding may not be possible given differences in intervention intensity and content. Outcomes will be measured at baseline and at 6-week and 3-month post-randomisation. Qualitative methods including focus groups and individual semi-structured interviews will examine patient acceptability of the intervention and explore perspectives of patients, clinicians and funders on its potential future optimisation and implementation.

Study flow is illustrated in figure 1. This trial will adhere to the CONSORT extension for pilot and feasibility trials^21^ and the Standards for Reporting Implementation Studies (StaRI) Statement and was prospectively registered with the Australian New Zealand Clinical Trials Registry (CTRN12626000506392).

**Figure 1 F1:**
[figure not shown]
CONSORT 2025 flow diagram. CONSORT, Consolidated Standards of Reporting Trials; RISE, recovery, information, support and empowerment.

### Participants

Participants will be eligible if they are: (1) aged 18 years or older, (2) diagnosed with WAD grade II/III (no fracture/dislocation) within 12 weeks of RTI, (3) identified at medium or high risk of poor recovery on the WhipPredict risk screening tool^22^ and (4) have access to a mobile phone and reasonable reception. Participants using their own Garmin wearable device will also require a compatible smartphone to operate the associated application (Fitrockr app).

Participants will be excluded if they: (1) demonstrate severe acute psychological distress or safety risk (Kessler Psychological Distress Scale (K6) >13^23^ and psychological risk screening) requiring a higher level of mental healthcare than can be safely provided within the trial intervention; (2) have relevant medical co-morbidities (ie, WAD Grade IV, fracture or injuries to other body areas or recent spinal surgery in the past 12 months or a pre-existing chronic pain condition); (3) are unable to complete study procedures in English or (4) do not have mobile phone access.

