#### Psychological distress

Non-specific psychological distress will be assessed using the K6.^23^ It is used during screening to determine the presence of acute psychological distress that would preclude involvement in the study and will be repeated at follow-up time points. Items are measured on a 5-point Likert scale, ranging from 1 (‘All of the time’) to 5 (‘None of the time’) and ask participants to indicate how they have been feeling during the past 30 days (eg, how… nervous, hopeless, restless/fidgety, worthless, that everything was an effort).

The Credibility/Expectancy Questionnaire^33^ assessed at baseline will measure how much participants believe that the intervention will help to improve their recovery. The measure is based around two key aspects of *belief:* (1) what one *thinks* will happen and (2) what one *feels* will happen. Participants will answer 2 sets of questions. Set 1 comprises four questions, three of which are scored on a 9-point scale ranging from 1 (‘Not at all logical’) to 9 (‘Very logical’). Questions include, “At this point, how successfully do you think this intervention will be in reducing your [pain/stress] symptoms?” The last question in Set 1 asks, “By the end of the intervention period, how much improvement in your pain/stress symptoms do you think will occur?” and is answered as a percentage, ranging from 0 to 100%. Set 2 comprises two questions about how participants feel about the intervention and its likely success answered on the same 9-point scale.

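### The K6 item coding as stated runs opposite to the K6 >13 exclusion, so the K6 component of the distress screen is inverted as written

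*Protocol article*

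**What the plan says.** The first exclusion criterion in the Participants section concerns "severe acute psychological distress or safety risk (Kessler Psychological Distress Scale (K6) >13". The sentence continues "and psychological risk screening) requiring a higher level of mental healthcare than can be safely provided within the trial intervention". A K6 total above 13 is therefore offered as a marker of severe distress, next to a second screen whose content and decision rule the article does not give.

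The Psychological distress section describes the same instrument in the same role: "It is used during screening to determine the presence of acute psychological distress that would preclude involvement in the study". On the response format it says "Items are measured on a 5-point Likert scale, ranging from 1 (‘All of the time’) to 5 (‘None of the time". The item content it lists is "nervous, hopeless, restless/fidgety, worthless, that everything was an effort", all of them symptoms.

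Table 1 schedules the K6 at screening and again at week 6 and 3 months. The article gives no reverse-scoring step, summing rule, total range or direction for the K6.

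**The concern.** The two sections assign opposite directions to one score. Under the exclusion, a higher total means a more distressed person. Under the item coding, a person who endorses a symptom more often gets a lower number, so a higher total means a less distressed person.

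The K6 cut-off is the only numeric element in the criterion that keeps out people who need more mental healthcare than the trial can safely provide. If the form were scored exactly as the article describes, that element would point the wrong way. The Trial oversight section dispenses with a Data Safety Monitoring Board on grounds of relatively low risk, so screening carries some weight here.

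A smaller consequence concerns follow-up. The Data analysis section plans between-group differences with 95% CIs for patient-reported outcomes. With the direction undefined, the sign of a K6 difference could not be read.

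**Working it through.** **Inputs**
- Cut-off: total >13 marks severe distress (Participants, exclusion 1).
- Item codes: 1 = 'all of the time' to 5 = 'none of the time' (Psychological distress). The article labels only these two ends. The three intermediate categories are called codes 2, 3 and 4 here.
- Number of items: six. This is an assumption from the name K6, since the text lists five examples. Five items are checked below.
- Scoring: a simple sum, also an assumption, since no rule is stated.

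**Step 1: apply the stated coding.** With six items the total runs from 6 × 1 = 6 to 6 × 5 = 30. For someone giving the same answer throughout:

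| Answer on every item | Total | >13? |
|---|---|---|
| Code 5, 'none of the time' | 6 × 5 = 30 | flagged |
| Code 4 | 6 × 4 = 24 | flagged |
| Code 3 (midpoint) | 6 × 3 = 18 | flagged |
| Code 2 | 6 × 2 = 12 | not flagged |
| Code 1, 'all of the time' | 6 × 1 = 6 | not flagged |

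Under >13 a total of exactly 13 is not flagged, so the unflagged totals are 6–13. The cut-off does not select the severely distressed under the stated coding.

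**Step 2: express this as distress.** Let D be the distress sum with each item scored 0 (none) to 4 (all of the time), so that D runs from 0 to 24. The total as stated is then 30 − D. The rule 30 − D > 13 gives D < 17. The K6 component flags everyone with D of 0–16 and passes everyone with D of 17–24.

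**Step 3: vary the number of items.** With five items the uniform totals are 25, 20 and 15 (flagged), then 10 and 5 (not flagged). The pattern is the same.

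**Step 4: see whether reversing the direction is enough.** Two codings in which high means more distress are compared. The 0–4 version is an assumed alternative that the article does not mention.
- Reversed 1–5 items: total = D + 6 (range 6–30). The rule D + 6 > 13 gives D > 7, so D of 8–24 is flagged.
- 0–4 items: total = D (range 0–24). The rule D > 13 flags D of 14–24.

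The two versions disagree for everyone with D of 8–13. A person answering at the midpoint throughout scores 18 on reversed 1–5 items (flagged) and 12 on 0–4 items (not flagged). In the other direction, >13 on the 0–4 base corresponds to >19 on the reversed 1–5 base. A reader who spots the direction problem still cannot recover the intended rule from the article.

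**The case against.** The strongest reply is that the K6 is not the whole criterion. It sits in a parenthesis beside a psychological risk screening, and the sentence ends by requiring a need for more care than the trial can give. Someone answering 'none of the time' throughout shows no severe distress and no such need, so reading the full sentence would probably not exclude them. This stands. A reader might infer that the trial as written excludes the least distressed people and admits the most distressed. The article does not support that, because it does not say how the two screens combine, and safety risk is named as an alternative ground. What survives is that the most distressed respondents would not trigger the K6 component. If both screens must be positive, that alone could stop the criterion from applying to them.

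A second reply is that the section describes response options, not a scoring algorithm. A form can be numbered one way and scored another, and an article commonly leaves scoring detail to the full protocol. This stands in part: reverse-scoring may be applied elsewhere, in which case the fault is one of reporting. Absence of a total range would not by itself be a finding. The article does, however, print explicit item codes and an explicit cut-off, and the two conflict.

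It is also tempting to suppose that an automatic REDCap score would apply the inverted rule. The article says that eligibility is screened by telephone and mentions REDCap for consent, the baseline survey, randomisation and outcome collection. It nowhere says that the screening K6 is scored electronically, so this should not be asserted.

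Finally, the follow-up consequence is minor. No hypothesis testing is planned, and the progression criteria in Table 2 do not use the K6.

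**Conclusion.** The contradiction is real and confined to the K6 component of the first exclusion. Taken as written, that component flags distress sums of 0–16 and misses 17–24 on a 0–24 scale, the reverse of its stated purpose. This rests on a simple sum of six items; the uniform-answer pattern is the same with five. Whether anyone would be wrongly admitted or excluded cannot be determined from the article, because the rule for the second screen is not given and reverse-scoring may exist outside it.

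Correcting the direction without naming the score range would leave the group with distress sums of 8–13 undetermined between the two codings compared. The point deserves correction before screening because it touches a safety criterion and is cheap to resolve. No view is taken on which cut-off is clinically right.

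**What to change.** Reconcile the Participants and Psychological distress sections. State one item coding, its direction, the resulting total range, and the range to which the exclusion cut-off refers. If reverse-scoring is already applied, say so where the response options are described.

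Check that the telephone screening form, and any electronic scoring that is used, match this definition before screening. Use the same coding for the K6 at 6 weeks and 3 months, so that the sign of a between-group difference is defined.

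The cost is a wording correction and one check of the form and scoring. No procedure, visit or sample size changes.

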### Procedure

#### Pre-enrolment

Potential participants recruited from the EDs will be identified by the triage nurse, doctor or staff delegate either in real-time during triage or patient consultation or on retrospective review of weekly ED presentation lists. Patients identified in real-time will be informed of the study, provided the study flyer and asked to provide verbal consent to be contacted by a member of the research team. Patients identified via retrospective review will be initially contacted via phone (PAH, Sunshine Coast) or via email or SMS (virtual ED site VECS) by site staff to seek verbal consent for the research team to contact them. Contact will be attempted up to three times, and if no contact is made, site staff will send the patient a letter inviting them to initiate contact with the research team if they would like to participate. At trial commencement, ED patient lists will be reviewed to identify potential participants who presented to the ED within the previous 12 weeks. Potentially eligible patients will be contacted in order of referral date, from oldest to newest, to maximise the likelihood of enrolment within the 12-week eligibility window. Recruitment will also involve flyer distribution to the general community (eg, through newsletters, clinic waiting rooms), digital marketing (including social media, paid Google Ads and email distribution methods) and participant referrals from other relevant research studies.

#### Screening and informed consent

Interested individuals will be screened for eligibility via telephone and informed about the study. Eligible participants will receive the Participant Information and Consent Form and provide informed consent electronically via REDCap (https://redcap.health.uq.edu.au). Ineligible individuals will be informed of the reason for ineligibility, offered the option to be contacted for future studies and provided with My Whiplash Navigator^24^ information and advised to consult their general practitioner for distress or pain management where required.

#### Baseline assessment, randomisation and onboarding

Participants who consent to participate will be asked to complete a baseline assessment survey via the REDCap system. Participants who complete the baseline survey are then randomised 1:1 into either the treatment (RISE intervention) or active control condition.

#### Overview of intervention period

Participants in both conditions will receive a welcome message 2 days after the baseline survey is completed to confirm enrolment and maintain contact while onboarding procedures are completed. Participants allocated to the RISE intervention will also be contacted by telephone to confirm their preferred messaging times and where applicable to organise the delivery of the wearable device (Garmin or Empatica EmbracePlus; device type dependent on availability) prior to commencement of the intervention. Instructions for setting up and using the device will also be provided. Participants will be instructed to wear the wearable device as much as possible over the entire intervention period, except when charging, as we are interested in both activity and sleep data. Participants in the RISE group will also be advised of the interactive nature of the intervention, including two-way messaging features, and offered optional support phone (audio-only) sessions during the intervention period, including one 30-min telephone session with a psychologist (or provisional psychologist) and one 30-min telephone session with a physiotherapist trained in the delivery of simple stress management techniques. Sessions will be scheduled as required. These onboarding procedures ensure participants are prepared to receive the RISE intervention and wearable devices prior to message delivery.

Seven days after the baseline survey is completed, participants will begin to receive the onboarding text messages relevant to their assigned condition. This timeframe allows for participants to receive the smartwatch. The onboarding message series will be delivered over 2 days to minimise burden and information overload. These messages will inform participants that they can pause or withdraw from the study at any point by texting SNOOZE or STOP to the trial’s dedicated mobile number. The messages will also include information on the research team, on-demand messages, two-way messaging options and emergency contact details. Prior to commencement of daily messages, a message will be sent to confirm that the wearable device has been set up and is working.

Messages will commence on the first Monday following completion of onboarding to standardise intervention delivery cycles. Commencement of the daily messages will be delayed to the following Monday if the wearable device has not yet been received. Participants will then receive the RISE intervention, which includes receiving approximately one text message daily. Participants in the control condition will begin to receive general health information via text messages every 2 days to support participant masking. Participants in the RISE intervention group will receive daily tailored messages, including the option to engage in interactive two-way messaging, respond to check-in messages and use the weekly reflective diary entry feature. If scheduled, participants in the RISE intervention will complete their psychologist and physiotherapist support sessions during the intervention period. Both interventions will be delivered over a 3 week period following completion of onboarding, with the option of an additional 3 days of messaging support for participants in the RISE group.

